### 3.3 Secondary endpoints

- Glucose metrics in ICU: mean and median morning blood glucose concentrations; mean daily blood glucose concentration; incidence of moderate (40-70 mg/dl) and severe (<40 mg/dl) hypoglycemia during ICU stay; peak of blood glucose after correction of hypoglycemia; duration of hypoglycemia; number of hypoglycemic events per patient; minimum and maximum blood glucose concentration per day; time within blood glucose target range; blood glucose variability; hyperglycemic index. These parameters will be studied during ICU stay, with and without censoring at 90 days
- Mortality in ICU and in hospital, with and without censoring at 90 days
- Mortality 90 days post randomization
- Hospital length of stay, with and without censoring at 90 days
- Time to (live) discharge from hospital, with and without censoring at 90 days. Hospital non-survivors will be censored beyond the longest duration of hospital length of stay of the survivors.
- Time to final (live) weaning from mechanical respiratory support, with and without censoring at 90 days. ICU non-survivors will be censored beyond the longest duration of mechanical respiratory support of the survivors.
- The duration of ICU dependency (defined as the crude number of days with need for vital organ support and as the time to live discharge from ICU to account for death as competing risk), with censoring at 90 days
- The incidence of new infections during ICU stay, with and without censoring at 90 days. Two experts in infectious diseases, who will be blinded for study group assignment, will determine, in consensus, the presence of infection on admission to the ICU and the presence of infection acquired after randomization. They will make their decision on the basis of guidelines in the study protocol (see 13. Data handling).
- The need for tracheostomy during ICU stay, with and without censoring at 90 days
- Presence of clinical, electrophysiological and morphological signs of respiratory and peripheral muscle weakness during ICU stay in patient subgroups in selected centers, with and without censoring at 90 days

- New kidney injury during ICU stay, with and without censoring at 90 days: the presence or absence of new kidney injury during ICU according to modified KDIGO criteria (Kidney Disease: Improving Global Outcomes) (21, 22); proportion of patients in need of new initiation of renal replacement therapy in ICU; duration of renal replacement therapy in ICU; recovery from kidney injury

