### 1. Clinical assessment

In patients awake at day 7±1, day 14±1, day 21±1, day 28±1, and thereafter at ICU discharge, muscle function will be assessed with the Medical Research Council (MRC) sum score and a dynamometer will be used to measure handgrip strength. In selected centers, also clinical assessments performed as part of standard care will be recorded. The MRC sum score bilaterally evaluates strength in three upper (upper arm abductors, elbow flexors and wrist extensors) and three lower limb muscle groups (hip flexors, knee extensors and foot dorsal flexors) attributing a score between 0 and 5 (0: no contraction; 1: visible/palpable contraction without limb movement; 2: limb movement only with gravity eliminated; 3: limb movement is possible against gravity but not against resistance; 4: subnormal contraction against resistance; 5: normal muscle strength) to each of them, rendering a maximal total score of 60 (29). A cut-off of <48 has been shown to identify ‘significant weakness’ (30-32).

Handgrip strength will be measured provided that a minimum value of 3 is scored for both wrist extension and forearm flexion (28). Maximal inspiratory pressures will be recorded if monitored as part of standard care.

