## 9.3 Analysis

A Consolidated Standards of Reporting Trials (CONSORT) diagram will be reported.

For the primary and most secondary endpoints taking place during ICU stay, all data will be available. Of the secondary endpoints, some laboratory measurements may be missing. Missing data for one time point may be interpolated, by calculating the mean of the two neighbor measurements. In other cases, missing data will not be imputed.

All analyses will be done on intention to treat basis. In case of request for discontinuation of the study intervention by the patient or legal representative, this will be respected, but all data that are already collected will be analyzed.

The data file will be finalized and locked 90 days after inclusion of the last patient (except for the post ICU follow-up outcome parameters, as specified above). Discrete variables will be summarized by frequencies and percentages. Continuous variables will be summarized by use of either mean and standard deviation (SD) or median and interquartile range as appropriate. Results will be analyzed with the use of Chi-square testing, Student's t test or non-parametric testing (Wilcoxon rank-sum test, Van der Waerden test or Median test), as appropriate. Time-to-event effects will be documented by Kaplan-Meier plots with use of log-rank/Wilcoxon testing; the time-to-event effect size will be estimated with the use of Cox proportional hazard analysis provided the proportional hazard assumption is valid for the dataset. All time-to-event analyses will also be performed on data censored at 90 days. As death is a competing risk for duration of care outcomes, non-survivors will be censored beyond the longest duration of such care required for survivors.

All outcomes will be analyzed in an uncorrected manner as well as adjusted for baseline risk factors (including type and severity of illness, age, gender, body mass index, history of diabetes or not, center). For these analyses, P-values will be considered significant when at or below 0.05 without correction for multiple testing. To assess whether any eventual impact of the intervention on the primary and safety endpoints is affected by the baseline risk factor subgroup, interaction P-values will be calculated (logistic regression or Cox proportional hazard analysis as appropriate) with a threshold for significance of interaction set at a P-value of <0.1. These a

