  - Parenteral nutrition (kilocalories, amino acids, lipids and carbohydrates cumulatively administered during 1 day)
  - Enteral nutrition (kilocalories, amino acids, lipids and carbohydrates cumulatively administered during 1 day)
- Mechanical ventilation (Y/N)

- Tracheostomy (Y/N)
- VV ECMO (Y/N)
- Mechanical hemodynamic support (Y/N), type (VA ECMO, VAD (including Heartmate, HeartWare, Impella, Excor), IABP)
- Markers of renal function
  - Plasma urea and creatinine
  - Creatinine clearance
  - Urinary output (24 hours, or for the first day from ICU admission until the time of sampling)
- Markers of hepatic (dys)function/damage
  - Transaminases
  - $\gamma$ -glutamyltransferase
  - Alkaline phosphatase
  - Bilirubin (total/direct)
- Circulating cardiac biomarkers (in selected centers)
  - Troponin, CK-MB, CK
  - NTproBNP
- C-reactive protein
- Blood lactate (maximum value)
- Blood counts
  - Red blood cells count and hemoglobin level
  - Leukocyte count
  - Thrombocyte count
- SOFA score and the different components (respiration, coagulation, liver, cardiovascular, central nervous system, renal)
- Maximum temperature and minimum temperature
- Heart rate >90 per minute (Y/N)
- Minimum and maximum heart rate, need for cardiac pacing (Y/N), need for cardioversion (Y/N), presence of atrial fibrillation (Y/N); cardiac index, including minimum, mean/median and maximum value in patients with pulmonary artery catheter or other transpulmonary thermodilution device (PiCCO,...); mixed venous oxygen saturation (SvO2), including minimum, mean/median and maximum value in patients with pulmonary artery catheter (in selected centers)
- Respiratory rate >20 per minute or arterial CO2 pressure <32mm Hg (Y/N)
- ICSDC score (worst observation during the day) in selected centers
- MRC-sum score and handgrip strength in selected centers (at day 7±1, day 14±1, day 21±1, day 28±1 and last day in ICU). The 'last day in ICU' measurement will only be recorded in patients having undergone a previous assessment.

- In selected centers: ICU mobility scale score at day 7 $\pm$ 1, day 14 $\pm$ 1, day 21 $\pm$ 1, day 28 $\pm$ 1 and last day in ICU. The 'last day in ICU' assessment will only be recorded in patients having undergone a previous assessment.
- In selected centers: electrophysiological assessment at day 14 $\pm$ 1, day 21 $\pm$ 1 and day 28 $\pm$ 1 in ICU

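### Handgrip strength is measured only in awake patients who pass a post-randomization strength gate, and no rule scores those who fail it, so a comparison between arms would tend to understate a true effect

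*Protocol*

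**What the plan says.** Protocol section 6.4, item 1 (Clinical assessment), sets who is assessed and when: "In patients awake at day 7±1, day 14±1, day 21±1, day 28±1, and thereafter at ICU discharge, muscle function will be assessed". The tools are the MRC sum score and, for grip, a dynamometer. The dynamometer has its own condition: "Handgrip strength will be measured provided that a minimum value of 3 is scored for both wrist extension and forearm flexion". The scale printed there defines the threshold score as "3: limb movement is possible against gravity but not against resistance". An awake patient who scores 0, 1 or 2 at either site therefore has no grip value.

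The MRC sum score has no such condition. For that score the section adds: "A cut-off of <48 has been shown to identify ‘significant weakness".

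The endpoint that these measures serve is in section 3.3: "Presence of clinical, electrophysiological and morphological signs of respiratory and peripheral muscle weakness during ICU stay in patient subgroups in selected centers". Section 13 lists "MRC-sum score and handgrip strength in selected centers" for the CRF. It lists neither the individual MRC items nor a code for a patient who was too weak for the dynamometer.

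On missing values, section 9.3 first notes that some laboratory measurements may be absent. It then says "Missing data for one time point may be interpolated, by calculating the mean of the two neighbor measurements", and continues: "In other cases, missing data will not be imputed". The tests it lists for continuous variables include the Wilcoxon rank-sum test.

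**The concern.** A patient below the gate has no grip value because he or she is weak, which is the state the measure is meant to detect. The gate is applied after randomization, and muscle weakness is one of the outcomes on which the arms are compared. Passing the gate can therefore depend on treatment, and the measured patients in the two arms need not be comparable even though the randomized groups were.

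The direction can be foreseen. If one strategy prevents severe weakness, more of its borderline patients become measurable, and they enter its arm with low values. Their counterparts in the other arm stay unmeasured. The better arm's measured average is pulled down, and a real difference looks smaller than it is.

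The interpolation rule does not help, even if it is read to cover handgrip. A patient too weak on one day but measurable on the visits either side would be given the mean of two stronger days.

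**Working it through.** **Inputs from the protocol.** The gate (both scores at least 3), assessment of awake patients only, the no-imputation default and the list of tests are given. The protocol states no handgrip SD, effect size, sample size or share below the gate, so there is no planned figure to reproduce. Every input below is an assumption.

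**Step 1: uniform benefit.** Let latent strength be normal with SD 1, mean 0 in controls and mean d in the treated arm. A patient is measured only if a gate score exceeds c. The gate score has correlation ρ with grip, and c is set so that a share q of controls falls below it. The mean grip among measured patients in an arm with mean μ is

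μ + ρ·λ(c − μ), where λ(a) = φ(a) / [1 − Φ(a)].

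The measured-only difference is therefore d + ρ·[λ(c − d) − λ(c)].

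Example with d = 0.30, q = 20% and ρ = 1:
- c = −0.8416
- λ(c) = 0.3500 in controls
- λ(c − d) = λ(−1.1416) = 0.2381 in the treated arm
- difference = 0.30 + 0.2381 − 0.3500 = 0.188 SD
- share of treated patients unmeasured = Φ(−1.1416) = 12.7%, against 20% of controls

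Results for d = 0.30 SD:

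| Controls below gate | ρ = 1.0 | ρ = 0.8 | ρ = 0.5 |
|---|---|---|---|
| 10% | 0.226 | 0.241 | 0.263 |
| 20% | 0.188 | 0.211 | 0.244 |
| 30% | 0.160 | 0.188 | 0.230 |

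At ρ = 1 the share of the effect lost is (0.30 − 0.226)/0.30 = 25%, then 37% and 47%. At ρ = 0.5 it is 12%, 19% and 23%. The sign does not change in any cell.

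**Step 2: power, for illustration.** Take 212 patients per arm. This is half of the 424 that section 6.4 gives for the electrophysiological comparison, so it is borrowed and not a handgrip sample size. With d = 0.30, ρ = 1 and a two-sided rank test at 5%, simulated power among measured patients is about 71%, 58% and 46% for 10%, 20% and 30% below the gate. Giving unmeasurable patients the lowest rank yields about 84–85%. Repeat runs agreed to within about 2 percentage points.

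**Step 3: benefit only near the gate.** Assume a mean of 18 kg in patients above the gate, a true grip of 3 kg in those below it, and 8 kg in those whom treatment lifts just above it. Let q be the share of controls below the gate and r the share of all patients lifted.

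- True difference = r × (8 − 3)
- Measured-only difference = [(1 − q) × 18 + r × 8] / (1 − q + r) − 18

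With q = 20% and r = 5%, the true difference is 0.05 × 5 = +0.25 kg. The measured-only difference is (14.4 + 0.4)/0.85 − 18 = −0.59 kg. Across q from 10% to 40% it runs from −0.53 to −0.77 kg. Scoring unmeasurable patients as 0 kg gives 0.05 × 8 = +0.40 kg, which restores the sign. In this pattern the sign reverses, but only because nobody else benefits and the lifted patients land just above the gate.

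**The case against.** The strongest reply has five parts.

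- **No handgrip analysis is specified.** Section 3.3 names the presence of signs of weakness as the endpoint, not kilograms of grip, and section 9.3 lists only generic tests. This stands as a limit on importance. Handgrip is nevertheless collected for the CRF, and the protocol's general rules would apply to any comparison made with it.
- **The weakest awake patients are still counted.** The MRC sum score has no strength gate, and low wrist or forearm scores lower it. This stands. A reader might infer that the plan loses its weakest patients from the weakness endpoint altogether; the documents do not support that.
- **The no-imputation sentence follows a remark about laboratory values.** It is arguable whether a test omitted by design counts as missing data. The sentence is worded generally, however, and no other rule in the protocol covers these patients. The SAP is not shown and may set one.
- **All magnitudes are assumed.** This stands. A reader might also infer that the gate would make a better arm look worse. A uniform benefit only shrinks; reversal needs benefit concentrated near the gate, and the protocol gives no reason to expect that pattern.
- **The reason for an absent value may not be recoverable.** It is tempting to assume that the recorded MRC items already show who was too weak. Section 13 lists only the sum score for the CRF, so the reason has to be recorded. Neurological and trauma patients are enrolled, and some will fail the gate because of a focal deficit and not generalized weakness.

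**Conclusion.** The point holds in a limited form. A handgrip comparison under the protocol's own rules would be conditional on a post-randomization strength outcome, and the foreseeable consequence is an understated effect. With an assumed uniform benefit of 0.30 SD and a gate that tracks grip closely, about 0.23, 0.19 or 0.16 SD remains when 10%, 20% or 30% of controls are below the gate. With a correlation of 0.5 it is 0.26, 0.24 or 0.23 SD. Sign reversal is a special case and should not be presented as the expected result.

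The matter bears on a supporting measure within a secondary endpoint in selected centers. It does not touch the primary endpoint or the MRC-based assessment of weakness. It deserves correction because the remedy is cheap and the bias is built into the measurement rule.

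**What to change.** Leave the measurement gate as it is. In sections 6.4, 9.3 and 13, or in the SAP:

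1. Add a CRF reason code for each absent handgrip value. It should separate too weak (wrist extension or forearm flexion below 3) from other reasons, such as not awake or a pre-existing or focal deficit.
2. Give awake patients coded as too weak the lowest rank, and compare arms with the Wilcoxon rank-sum test that section 9.3 already lists.
3. Report the proportion too weak to test in each arm.
4. Label the values from measured patients alone as descriptive.

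The cost is a sentence or two of text and one CRF field. There are three downsides. The comparison is in ranks and not kilograms. It has little power if benefit is confined to patients near the gate (roughly 5–24% in simulations of that pattern), which is why the proportion too weak must be reported beside it. And it does not remove the selection that comes from being awake and still in the ICU at the assessment days.

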## 2. Electrophysiological tests

Electrophysiological tests will be performed at day  $7 \pm 1$ , day  $14 \pm 1$ , and day  $21 \pm 1$  in ICU. *Repetitive nerve stimulation* of the abductor digiti minimi muscle of the hand is performed at 3 Hz to evaluate the neuromuscular junction. *Nerve conduction studies* to evaluate the presence of peripheral neuropathy or myopathy include measurement of compound muscle action potential (CMAP) of the anterior tibial and abductor digiti minimi muscle and of sensory nerve action potential (SNAP) of the little finger under supramaximal stimulation with a hand-held stimulation probe. Presence of edema is scored. *Needle electromyography* (EMG) is performed in the resting condition in the tibialis anterior, rectus femoris, extensor digitorum communis and deltoideus pars media muscles to evaluate the presence of abundant spontaneous electrical activity (SEA), defined as the presence of sustained fibrillation potentials and/or positive sharp waves. *Direct muscle stimulation* of the tibialis anterior muscle is performed as previously described to differentiate between myopathy and neuropathy (33). The stimulation electrode is placed near the lower third of the tibialis anterior muscle. The recording electrode is positioned 30mm proximal to the stimulation electrode, guided by the twitch and depth at which maximal amplitude is obtained. Both stimulating and recording electrodes are repositioned until maximal response is obtained. Compound muscle action potential amplitudes generated after direct muscle stimulation (dmCMAP) are measured peak to peak. With the same recording electrode in place, the deep peroneal nerve is stimulated at the head of the fibula and the resulting motor response is recorded (nerve-stimulated CMAP, neCMAP). The ratio of neCMAP/dmCMAP will be calculated. These tests will be performed on the contralateral side of the eventual biopsy (see below). Also data obtained by electrophysiological tests performed as part of standard care will be recorded in selected centers.

## 3. Ultrasound

In selected centers, ultrasound of the quadriceps muscle and the diaphragm will be performed at day  $7 \pm 1$ , day  $14 \pm 1$ , and day  $21 \pm 1$  in patients still in the ICU at these time points. For ultrasound of the quadriceps muscle, a linear array commercial real-time ultrasound scanner will be used with a 12-MHz transducer. Ultrasonographic images will be collected from a transversal scan of the thigh with the patient in the supine position, with the knee extended and the muscle relaxed. The transducer will be placed perpendicular to the long axis of the thigh on three-fifths of the distance from the anterior superior iliac spine to the superior patellar border. This position will be defined beforehand with a surgical skin marker after measuring the exact position with a tape measure. An excess of contact gel will be applied to minimize image distortion. By obtaining maximal reflection of the bone, optimal transducer orientation is achieved and oblique scanning is minimized. All images will be

analyzed directly on the ultrasound scanner. The probe will be angled to obtain the highest density in the cortical bone of the femur. Then the pressure on the probe will be gradually released up to the point where the view on the outer margins is lost. At this point of minimal pressure, the muscle thickness in the center of the view will be measured. Muscle thickness will be defined as the distance between the superior border of the muscle and the cortex of the femur. Each limb will be measured. If feasible, also cross-sectional area of the quadriceps femoris, ultrasound intensity and pennation angle will be quantified.

For ultrasound of the diaphragm, the patient is positioned head-end of the bed 30° up. A 4-12 MHz linear array transducer is positioned at the zone of apposition between the anterior and mid-axillary lines at the level of the 9th or 10th intercostal space and angled perpendicular to the chest. The diaphragm is identified a three-layered structure just superficial to the liver, as a relative non-echogenic muscular layer, bounded by the echogenic membranes of the diaphragm pleura and peritoneum. After visualisation, the probe position is marked. Patients are assessed while receiving ventilator settings as set by the treating physician in case of assisted or controlled mechanical ventilation. For patients breathing spontaneously, the PS level is set to obtain TV 6-8ml/kg IBW, ensuring comfortable breathing. Measurements of end-expiratory thickness (Tdi,ee) and the following end-inspiratory thickness (Tdi,ei) are performed during 3 respiratory cycles. Diaphragm thickness is measured as the distance between the diaphragmatic pleura and the peritoneum using the M mode. Thickening fraction is calculated as  $TF_{di} = (T_{di,ei} - T_{di,ee}) / T_{di,ee}$  for each of the three respiratory cycles, average value of these three calculations will be used for analyses. After the procedure, the mark is covered with a transparent cover that remains in place until the next measurement. In selected centers, ultrasound of the diaphragm will also be performed at baseline (day 0 or 1). Also data obtained by ultrasound of the diaphragm as performed as part of standard care will be recorded.

#### 4. Functional tests

Patients will be scored on the ICU mobility scale at day 7±1; day 14±1, and day 21±1 in ICU. In these patients, the ICU mobility scale will also be assessed at ICU discharge. This score represents a functional evaluation of the patient and varies from 0 to 10. Whereas a score of 0 represents a patient who is unable to move (lying in bed), score 10 represents a fully mobile patient (defined as walking at least 5 meters independently without a gait aid or assistance from another person) (34).

#### 5. Muscle biopsy

To correlate the clinical and electrophysiological findings to cellular changes, a small muscle and fat biopsy will be harvested at day 7±1, day 14±1, and day 21±1 in ICU. This will enable the study of the underlying cellular and molecular mechanisms leading to ICU-acquired muscle weakness and potentially other ICU complications. A quadriceps (vastus lateralis) needle biopsy will be taken under local anesthesia. Biopsies will not be obtained in patients with increased bleeding risk (platelet count <50000/μl, PT<40%, receiving anticoagulant

treatment or other bleeding diathesis). The skin is disinfected and sterile dressings are applied. Skin, subcutaneous tissues and muscle are infiltrated with lidocaine 2% solution via a 21 gauge injection needle. After 5 minutes, a 5 mm skin incision is made with a # 23 surgical blade (Swann-Morton). Subsequently, the needle biopsy will be taken in a sterile manner with a 5 mm Bergstrom needle. The subcutaneous adipose tissue of the quadriceps muscle biopsy will be stored separately. After manual hemostatic compression, the skin incision is closed with Steristrips™ (Nexcare™) skin closure adhesive strips and covered with a sterile transparent wound dressing. A compressive bandage is applied for 8 hours. An information letter with instructions for aftercare will be given to the nurse. In the muscle and subcutaneous adipose tissue, we will map crucial mediators of the different (epi)genetic, inflammatory, endocrine and metabolic pathways (depending on additional funding).

Depending on additional funding, additional investigations will be performed on the stored blood, urine and drainage fluid samples to unravel the metabolic, endocrine, inflammatory, immunological and (epi)genetic pathways involved in mediating organ dysfunction.

In selected centers, survival status will be investigated up to 4 years post randomization by consulting the National Registry (Rijksregister) or by other means for foreigners (checking the medical files). Depending on additional funding and in selected centers, subgroups of patients will be reinvited for a 1-2 yearly follow-up consultation up to 4 years post randomization. At that time point, recovery of organ function, functional status and muscle strength will be investigated by clinical history taking and clinical assessment, eventually supplemented by laboratory tests, questionnaires, functional testing and/or muscle biopsies. The protocol and informed consent for any follow-up investigation that is not routinely performed will be filed in an amendment of the current protocol.

